**Fig. 1 Fig1:**
[figure not shown]
Flowchart of study procedure during multidisciplinary team meeting

#### Intra-operative imaging and histological findings

During surgery, intraoperative ultrasound (IOUS) of the liver is performed by the surgeon or the radiologist followed by the actual surgical or ablative treatment. IOUS is not part of the primary aim of this study and is performed especially to determine surgical margins and identification of vascular structures and not primarily for lesion detection and characterization. We will register whether IOUS has found new CS-CRLM in addition to the preoperative CT and liver MRI, and whether the findings of the IOUS changed the surgical or ablative plan. Additionally, we will strive to report whether postoperative histopathology reports were in accordance with findings of the pre-operative CT, liver MRI and IOUS.

### Follow-up

All patients who underwent surgical and/or ablative treatment will be assessed in the local follow-up schedule of the study site. Ideally, patients will be seen with a CT-chest/abdomen at 3 to 4 months and 6 to 8 months after surgery and/or thermal ablation. Patients who are no longer considered as candidates for local curative therapy based on the additional liver MRI findings will have at least 6 months follow-up by CT, as stated in ESMO guidelines^13^. Findings regarding disease recurrence or new CRLM, possible treatment options and overall patient survival will be documented during at least 6 months follow-up.

### Expert panel procedure and evaluation

In addition to the primary outcome measure which will be determined in the daily clinical workflow of the participating centres, a fixed central independent, blinded expert panel is created to validate the findings of the individual centres as a secondary outcome measure. The expert panel consists of three abdominal radiologists, two interventional radiologists and three liver surgeons. These are recruited from participating centres and will post-hoc evaluate step-by-step the additional value of liver MRI as compared to CT only on the local therapy plan. The participating radiologists have extensive experience with CT and liver MRI and have assessed at least 500 abdominal CT scans and 500 liver MRI scans for focal liver lesions. The participating liver surgeons performed at least 100 liver resections. The participating interventional radiologists have extensive experience in performing thermal ablation of CRLM and performed at least 100 liver ablation procedures. The CT and liver MRI of each patient will be assessed by one radiologist only since all radiologists have extensive experience in assessing abdominal CT scans for focal liver lesions and liver MRI scans. Radiologists will not review examinations from their own centre. Based on CT and liver MRI findings of the radiologist, each interventional radiologist and surgeon will get the findings presented and will indicate independently whether they would change their initial local therapeutical plan based on the liver MRI results. Agreement of 4/5 expert panel members (agreement rate of 80% or more) will be considered as consensus. In case of agreement of three or less expert panel members, a joint consensus meeting will be organized to discuss the respective cases and eventually reach consensus.

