### Study outcomes

The primary outcome of the current study is the proportion of patients with a change in local therapy plan due to CS-CRLM on liver MRI, not seen on CT. CS-CRLM are defined as liver lesions that have not been incorporated in the initial resection and/or ablation plan based on CT, hence leading to a change in local therapy. Change in local therapy is defined as any change in surgery or thermal ablation including increase or decrease of the number or extent of liver resections, increase or decrease in number of ablation zones, surgery to ablation, ablation to surgery, addition of ablation to surgery and cancellation of local therapy. The local therapy plan proposed by the MDT based on CT only will be compared to the local therapy plan based on CT and liver MRI.

Secondary outcomes include a prediction model to evaluate the probability of finding CS-CRLM on liver MRI and the proportion of patients with a change in local therapy plan based on the occurrence of CS-CRLM on liver MRI, as identified by the expert panel in the post hoc evaluation.

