### Statistical analysis plan

Since the CAMINO study has a pragmatic design and should represent daily clinical practice, the main analysis of the primary outcome will be based on the intention-to-imaging (ITI) population. The ITI population will consist of all included patients fulfilling the inclusion criteria of the CAMINO study, regardless of any study protocol violation such as an extended time interval of more than 4 weeks between CT and MRI and liver MRI performed with another contrast agent then Gadoxetic acid. The incremental accuracy in the ITI analysis will be calculated as the number of included participants with a clinically significant CRLM (CS-CRLM) detected by liver MRI and not seen on CT, as identified by the local MDT, relative to the total number of included participants.

Additionally, the main analysis will be complemented by an imaging-per-protocol (IPP) analysis. The IPP population will include all patients fulfilling the inclusion criteria and undergoing all study procedures per study protocol, excluding patients who showed any study protocol violation or deviation. The incremental accuracy in the IPP analysis will be calculated as the number of included participants with a clinically significant CRLM (CS-CRLM) detected by liver MRI and not seen on CT, relative to the total number of included participants without .

Three subgroup analyses will be performed: first, in the groups of patients who did and did not receive preoperative chemotherapy; second, in patients who did and did not undergo a FDG-PET-CT, and at last, based on the number of CRLM.

A prediction model will be developed using multivariable relaxed lasso logistic regression modelling, to evaluate the probability based on patient, tumor and procedural variables of finding CS-CRLM on liver MRI. This exploratory model will be used for identifying subgroups in whom the probability of finding CS-CRLM is less than 10%. All baseline variables will be considered for the regression model.

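### The expert panel votes on any MRI-driven plan change, but the panel outcome counts only changes due to CS-CRLM, and no stated step links the two

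*Protocol article*

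**What the plan says.** The section 'Expert panel procedure and evaluation' of the protocol article sets up a panel of "three abdominal radiologists, two interventional radiologists and three liver surgeons". The abdominal radiologists supply the findings: "The CT and liver MRI of each patient will be assessed by one radiologist only". Those findings go to the two interventional radiologists and three surgeons, each of whom "will indicate independently whether they would change their initial local therapeutical plan based on the liver MRI results". The decision rule is: "Agreement of 4/5 expert panel members (agreement rate of 80% or more) will be considered as consensus". With three or fewer agreeing, the case goes to a joint meeting.

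'Study outcomes' sets the quantity that the panel is to deliver. It is a patient-level proportion, and the event counted is: "change in local therapy plan based on the occurrence of CS-CRLM on liver MRI, as identified by the expert panel in the post hoc evaluation". CS-CRLM are "liver lesions that have not been incorporated in the initial resection and/or ablation plan based on CT", so that the therapy plan changes because of them.

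The local figure that the panel is set against is defined in 'Statistical analysis plan'. It counts participants with a CS-CRLM "detected by liver MRI and not seen on CT, as identified by the local MDT, relative to the total number of included participants". 'Multidisciplinary team meeting' has the centre document a CT-based plan first, and then both the CS-CRLM found and the exact change to the plan.

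**The concern.** The vote and the outcome differ in cause. The vote accepts any MRI result as the reason for a change; the outcome accepts one reason only. A voter who would plan less because MRI reclassifies a CT lesion as benign answers 'yes', and so does one who re-plans because a known lesion looks larger. Neither change is due to a lesion left out of the CT-based plan. Nor does the four-of-five rule require the agreeing voters to have the same lesion in mind.

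Such cases are not caught later. The joint meeting is triggered by lack of agreement, so four 'yes' votes given for another cause, or for different lesions, are settled without discussion.

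This matters because the panel is the study's check on what the centres report, and the 'Discussion' relies on it to interpret variation between observers. If the panel answers a broader question than the centres, a gap between the two proportions cannot be put down to readers alone.

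**Working it through.** **The plan's own figure.** Voters: 2 interventional radiologists + 3 surgeons = 5. Threshold: 4/5 = 80%. This agrees with the text; the problem is one of definition, not arithmetic.

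**The two statements side by side.**

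| | Panel vote ('Expert panel procedure and evaluation') | Panel outcome ('Study outcomes') |
|---|---|---|
| Trigger | MRI results in general | Occurrence of CS-CRLM on MRI |
| Stated answer | Whether the plan changes | Plan change attributable to such a lesion |
| Same lesion for agreeing voters | Not required | Not addressed |

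Every patient in whom four voters would change the plan because of a CS-CRLM also has four 'yes' votes, but the converse does not hold. The voted proportion is therefore at or above the proportion that the outcome defines.

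Other-cause changes are foreseeable from the article itself. 'Background' expects diffusion-weighted MRI to cut false diagnoses of metastases. The 'Discussion' notes that indeterminate MRI lesions can complicate planning. The list of changes in 'Study outcomes' includes decreases in resections and ablation zones.

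**Size.** Inputs: true CS-CRLM proportion p = 10% and n = 298 enrolled, both from 'Sample size calculation and statistical considerations'. The share x of patients with an MRI-driven change from another cause is not in the documents; the range of 1% to 5% is an assumption. All such changes are taken to reach four 'yes' votes and to be counted.

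SE = √(0.10 × 0.90 / 298) = 0.0174, or 1.74 percentage points.

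Voted proportion = 10% + x; extra events = 298x; shift in SE units = x / 0.0174; share of counted events that are truly CS-CRLM = 10 / (10 + 100x).

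| x | Voted proportion | Extra events | Shift (SE) | Truly CS-CRLM |
|---|---|---|---|---|
| 1% | 11% | 3.0 | 0.6 | 91% |
| 2% | 12% | 6.0 | 1.2 | 83% |
| 3% | 13% | 8.9 | 1.7 | 77% |
| 5% | 15% | 14.9 | 2.9 | 67% |

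At the 270 patients of the basic sample size the proportions are the same. With x = 5% the 95% Wald interval around 15% is 15% ± 1.96 × √(0.15 × 0.85 / 270) = 10.7% to 19.3%, which excludes the true 10%.

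**The case against.** Four arguments can be made on the other side.

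- **The article is condensed.** A full protocol exists, and the fields of a panel form are properly left to it. The review is described as stepwise, and the findings shown to the voters come from a radiologist's reading, so lesion-level data probably exist. This is fair as far as form fields go. But the article states the voters' question, the threshold and the route for split votes, and the question as stated is broader than the outcome.
- **The two sections can be read together.** 'Study outcomes' restricts the counted event to CS-CRLM, so a 'yes' vote could be combined with the radiologist's list of lesions seen only on MRI. That is possible, but no such rule is written. It would also leave mixed cases open, where a patient has both a new lesion and a reclassified one.
- **The outcome definition is itself wide.** It admits decreases and cancellations, so a loose reading narrows the gap. The requirement that the change arise from a CS-CRLM nevertheless remains.
- **The size rests on an assumed rate.** This stands in full.

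A reader might go further and infer that genuine new lesions are lost, because each voter judges against their own CT plan and some plans may already cover the site. The documents do not support this. CS-CRLM status depends on the plan: the abstract excludes new metastases in segments already due for resection, so 'no change' is the correct answer for a voter whose plan covers the lesion. Split votes go to the joint meeting and are not discarded. Suppose, for illustration, that each voter's plan independently covers the site with probability c = 10%, 20% or 30%. The chance of an outright 'no' (at least four of five) is 5c⁴(1 − c) + c⁵ = 0.05%, 0.7% or 3.1%. Judging against one's own CT plan is ordinary independent replication and suits the study of observer variation.

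**Conclusion.** The point holds for the cause of the change. As stated, the vote measures any MRI-driven change, while the outcome is a change due to a CS-CRLM. The stated rule can therefore only raise the panel proportion relative to its definition. With 10% true and an assumed 1% to 5% of patients having other-cause changes, the panel would return 11% to 15%. If such changes are rare, or are filtered out by a rule not shown here, the effect vanishes.

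Severity is minor. One secondary outcome and its use as a check on the centres are affected; the primary outcome determined by the local team and the sample size are not.

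**What to change.** In 'Expert panel procedure and evaluation', have each voter record two things: whether the plan changes, and which MRI lesion causes the change. Code the lesion as one of:

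1. a metastasis not seen on CT and not covered by that voter's own CT-based plan;
2. a CT lesion that MRI re-characterised or re-measured;
3. other.

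Apply the four-of-five rule to a change due to a lesion of the first kind. Send cases with at least four 'yes' votes but no common qualifying lesion to the consensus meeting already planned. Report changes from other causes as a separate proportion. No common CT plan needs to be imposed on the panel.

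The cost is a few fields on the panel form, a sentence in the counting rule and some more cases for the meeting. No extra patients, readers or procedures are needed. The panel proportion may come out somewhat lower than under the vote as now worded.

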### Study outcomes

The primary outcome of the current study is the proportion of patients with a change in local therapy plan due to CS-CRLM on liver MRI, not seen on CT. CS-CRLM are defined as liver lesions that have not been incorporated in the initial resection and/or ablation plan based on CT, hence leading to a change in local therapy. Change in local therapy is defined as any change in surgery or thermal ablation including increase or decrease of the number or extent of liver resections, increase or decrease in number of ablation zones, surgery to ablation, ablation to surgery, addition of ablation to surgery and cancellation of local therapy. The local therapy plan proposed by the MDT based on CT only will be compared to the local therapy plan based on CT and liver MRI.

Secondary outcomes include a prediction model to evaluate the probability of finding CS-CRLM on liver MRI and the proportion of patients with a change in local therapy plan based on the occurrence of CS-CRLM on liver MRI, as identified by the expert panel in the post hoc evaluation.

### Data collection

All parameters will be collected prospectively. Relevant patient data (e.g. patient characteristics, medical history, primary tumor information, local or recurrent CRLM, neoadjuvant chemotherapy, laboratory results, pathology report and follow-up data) will be retrieved from the electronic patient record. Imaging results will be collected according to a standardized radiology report, including the following parameters: number, size and localization of lesions, vascular involvement of lesion (i.e. involvement of portal and/or hepatic veins), characterization of lesions (i.e. indeterminant or definitely malignant). For MRI, the sequence on which the lesion was seen best will also be documented. Postoperative data will be obtained for 30 days, including complications, length of hospital stay, readmission and mortality. Participating centres are asked to collect and share their images of the pre-interventional CT chest/abdomen and liver MRI in order to be assessed by the expert panel. All patient data and imaging will be coded by an individual study number and saved in the eCRF. No identifying data will be entered into the database. All data and patient imaging will be stored in an online database specially designed to share patient imaging in a safe and privacy-respecting environment (ALEA®, FormsVision, Abcoude, the Netherlands). Safety reporting and a DSMB are not implemented in this study as there are no added risks. This study will follow the FAIR principles in handling and storage of data [34].

### Statistical analysis plan

Since the CAMINO study has a pragmatic design and should represent daily clinical practice, the main analysis of the primary outcome will be based on the intention-to-imaging (ITI) population. The ITI population will consist of all included patients fulfilling the inclusion criteria of the CAMINO study, regardless of any study protocol violation such as an extended time interval of more than 4 weeks between CT and MRI and liver MRI performed with another contrast agent then Gadoxetic acid. The incremental accuracy in the ITI analysis will be calculated as the number of included participants with a clinically significant CRLM (CS-CRLM) detected by liver MRI and not seen on CT, as identified by the local MDT, relative to the total number of included participants.

Additionally, the main analysis will be complemented by an imaging-per-protocol (IPP) analysis. The IPP population will include all patients fulfilling the inclusion criteria and undergoing all study procedures per study protocol, excluding patients who showed any study protocol violation or deviation. The incremental accuracy in the IPP analysis will be calculated as the number of included participants with a clinically significant CRLM (CS-CRLM) detected by liver MRI and not seen on CT, relative to the total number of included participants without .

Three subgroup analyses will be performed: first, in the groups of patients who did and did not receive preoperative chemotherapy; second, in patients who did and did not undergo a FDG-PET-CT, and at last, based on the number of CRLM.

A prediction model will be developed using multivariable relaxed lasso logistic regression modelling, to evaluate the probability based on patient, tumor and procedural variables of finding CS-CRLM on liver MRI. This exploratory model will be used for identifying subgroups in whom the probability of finding CS-CRLM is less than 10%. All baseline variables will be considered for the regression model.

All baseline, clinicopathological and procedural variables will be described and analysed. Continuous, not normally distributed variables will be expressed as median with interquartile range (IQR). In case variables are normally distributed they will be reported as mean with standard deviation (SD). A Mann-Whitney U test will be used to compare continuous, not normally distributed variables between groups. Normally distributed, continuous variables will be compared using an Independent samples T-test. Categorical variables will be reported as frequencies and proportions and compared between groups using a chi-square test. *P*-values below 0.05 will be considered significant. Data analysis will be performed using IBM SPSS Statistics for Windows© version 25.0 (SPSS Inc., Chicago, IL, USA).

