### Sample size calculation and statistical considerations

The literature on the clinical impact of additional liver MRI in patients with primary or recurrent CRLM is very limited and consists of primarily small retrospective studies [26, 35]. Our estimate of the chances of finding CS-CRLM on liver MRI is based on literature, clinical experience and practicality.

A smaller change in local therapy plan is expected than previous studies have shown, as CT technique and interpretation have evolved. Based on these considerations, the proportion of patients in which liver MRI finds CS-CRLM is postulated to be 10%. Such a proportion can be considered as a relevant impact on local therapeutical management.

The primary outcome measure, the proportion of patients with CS-CRLM on liver MRI not identified on CT, guides the sample size for this incremental diagnostic accuracy study. Taking into account that all patients will undergo CT and liver MRI, precision is defined as one-sided 95% confidence interval (CI) with a lower confidence bound of 6.5%. Sample size calculation indicated that 270 patients need to be included in order to obtain estimates of change in management in 10% with 95% CIs that does not exceed 7%.

A small subset of the patients will undergo FDG-PET-CT instead of CT. During a recent national meeting of the Dutch Liver Collaborative Group, an assessment about the use of FDG-PET-CT was performed and approximately 5% of patients in this study is expected to undergo FDG-PET-CT instead of CT. To adjust for patients that undergo FDG-PET-CT instead of CT, an increase of 5% of the desired number of participants is made, resulting in 284 patients. Given the design of the study, a maximum dropout of 5% is expected. Taken this dropout into account, a total of 298 patients must be enrolled in this study. If a participant withdraws consent, a new one will be recruited.

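### The below-10% subgroup rule sits at the postulated overall rate of 10%, so read in-sample it can name a false low-yield subgroup

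*Protocol article*

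**What the plan says.** The Statistical analysis plan section of the protocol article fixes three things about the prediction model.

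- The method is "multivariable relaxed lasso logistic regression modelling".
- The candidate pool is open: "All baseline variables will be considered for the regression model".
- The use is stated: "This exploratory model will be used for identifying subgroups in whom the probability of finding CS-CRLM is less than 10" per cent.

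The section on sample size gives the numbers behind it: "the proportion of patients in which liver MRI finds CS-CRLM is postulated to be 10" per cent, and "a total of 298 patients must be enrolled in this study". That sample size is driven by the precision of the primary proportion, not by the model.

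The model is a listed secondary outcome (Study outcomes) and serves the secondary aim of finding who benefits most (Objectives and hypotheses). The Discussion adds that the study may also show which patients do not benefit.

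**The concern.** The cut for a low-yield subgroup is the same number as the expected overall rate. A logistic model with a free intercept has an average predicted risk equal to the observed rate. If that rate is near 10%, any fitted model that is not constant spreads patients on both sides of the cut, whether the spread is signal or noise. A point prediction below 10% then says little more than that the patient is below average on the fitted score.

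With about 30 events and many candidates, part of that spread will be noise. The same data that chose the variables would also show a low event rate in the labelled group, so the subgroup would appear to confirm itself. At stake is a secondary conclusion that MRI yield in some patients is below what the article calls the minimal clinically important difference, when their true yield is the same as everyone else's.

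**Working it through.** **1. The plan's own sample size.** With p = 0.10 and a Wald bound, n = z²p(1−p)/d².

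- One-sided 95%, lower bound 7% (d = 0.03): 1.645² × 0.09 / 0.0009 = 270.6, which matches the stated 270.
- The other stated bound, 6.5% (d = 0.035), gives 199 one-sided or 283 two-sided, so 270 goes with 7%. This does not affect the present point.
- 270 × 1.05 = 283.5, rounded to 284. Then 284 × 1.05 = 298.2, rounded to 298.

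**2. Events.** 0.10 × 270 = 27 and 0.10 × 298 = 29.8. The number of candidates is not given. For an assumed 10, 20 or 30, that is 3.0, 1.5 or 1.0 events per candidate.

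**3. Why the cut falls at the mean.** The intercept equation of a logistic fit is Σ(yᵢ − p̂ᵢ) = 0, so the mean of p̂ equals the observed rate. This is exact for the lasso with unpenalised intercept and for the full refit, and approximate for a blend of the two. With 30/298 = 10.07% observed, the mean sits on the 10% cut. Predicted risks are right-skewed, so slightly more than half the patients tend to fall below. If no variable is selected, every patient gets the observed rate, so all or none are labelled.

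**4. Simulation with nothing predictive.** There were 298 patients, 30 events, 10-fold cross-validation and 500 data sets per scenario. Assumed inputs were 10, 20 or 30 independent candidates (half continuous, half binary, plus variants with mostly or only binary candidates) and three tuning rules. Label shares are given for data sets where at least one variable was selected.

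| Quantity | Result |
|---|---|
| Any variable selected, cross-validated minimum | 35–44% of data sets |
| Any variable selected, one-standard-error rule | 12–16% (2–3% in the runs with 24, 27 or 36 events) |
| Mean share labelled below 10% | 52–61% |
| 5th–95th percentile of share, mixed candidates | about 32–77% |
| 5th–95th percentile of share, binary only | about 18–87% |
| Apparent event rate in the labelled group | about 5–6% |
| True event rate in the labelled group | 10% |

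A separate simulation (30 candidates, 250 data sets) gave 32% with any selection, 54% labelled and an apparent rate of 5.0%. Another (30 candidates, 120 data sets) gave 40%, 56% and 5.6%.

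**5. Is relaxation the cause?** In that last simulation, plain lasso gave 40% with any selection, 53% labelled and an apparent rate of 5.4%, which is practically the same. Ridge never selects nothing. In a similar null simulation it labelled 46% of patients on average.

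**6. Dependence on the observed rate** (20 candidates, cross-validated minimum tuning). At a true 10%, the 95% range of observed events in 298 is 20 to 40.

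- 24 events: mean share labelled 71–81%.
- 36 events: 32–49%.
- True rate 20%: 4–12%. True rate 30%: at most 2%.

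**7. What a limit on the proportion would ask.** The two-sided 95% Clopper–Pearson upper limit is 9.9% for 4/100, 9.4% for 7/150 and 9.98% for 10/180. A null labelled group of 0.55 × 298 = 164 patients with an apparent 8 or 9 events (4.9% or 5.5%) has an upper limit of 9.4% or 10.2%. A limit computed on apparent counts would therefore pass some groups whose true rate is 10%.

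**The case against.** Several points on the other side stand.

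- The article calls the model exploratory, and its Discussion speaks only of an attempt. A reader might infer that MRI would be withheld on the strength of this model. The article says no such thing.
- The article condenses a full protocol that is not shown. A reader might infer that no optimism correction or validation is planned. Such detail is commonly left to the full document, so its absence here is not part of this point.
- It is tempting to blame the relaxed lasso for removing shrinkage. The degree of relaxation is itself a tuning choice, the ordinary lasso is nested within it, and step 5 shows the same labelling without it. Switching to plain lasso or ridge would not cure the problem.
- The 10% cut is a reasoned threshold, since it is the stated minimal clinically important difference and the hypothesis is for at least 10%. It coincides with the mean only if the result lands near that minimum.
- False labelling is not certain. With no signal, cross-validated tuning selected nothing in most data sets.
- With real predictors the label can be right on average. In a simulation with three (log-odds 0.5, 0.4 and 0.3 per SD), the low group's true risk was 7.5%, although it appeared as 4.6%.

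None of this removes the core. The article fixes an open candidate pool and a cut equal to the rate it postulates. At that rate, a point prediction below the cut does not separate a real low-yield subgroup from noise.

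**Conclusion.** The point holds in a conditional form. If the observed rate is near the postulated 10% and the model selects at least one variable, on average about half the patients (52–61% at 30 events) are labelled below 10%, even when nothing predicts. Single data sets vary widely around that average. With no true predictor, selection occurs in roughly 30 to 45% of data sets under cross-validated minimum tuning and less often under the one-standard-error rule. The labelled group then looks like 5–6% while its true rate is 10%.

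These figures rest on an assumed 10 to 30 independent candidates and assumed tuning rules, none of which the article gives. The effect largely disappears at a true rate of 20% or more. The documents do not support the stronger statement that half the patients will be mislabelled whenever any variable enters. Nor do they support a fixed ceiling on the number of parameters, which would need an assumed explained variation. This concerns an exploratory secondary outcome and leaves the primary analysis untouched. It should still be settled before the data are analysed.

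**What to change.** Keep the penalised model and change how the 10% cut is read.

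1. Limit candidates to variables known before MRI. The section names procedural variables among the predictors, and only those already fixed by the CT-based plan can inform who needs an MRI.
2. Repeat the whole procedure, including variable selection and tuning, within cross-validation or the bootstrap.
3. Call a subgroup below 10% only if the upper 95% limit of its cross-validated or optimism-corrected proportion is below 10%. The apparent proportion must not be used, for the reason in step 7 of the working.
4. Otherwise, report that no low-yield subgroup was shown.

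The cost is additional analysis work and no additional patients. The real downside is that the study may be unable to name a low-yield subgroup: as a guide, about 4 events in 100 patients or 10 in 180 is the most that would qualify.
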